## Abstract

**Introduction:**

Post-stroke depression (PSD), characterized by low mood and low interest, is the most common complication after stroke. The limitations of PSD drug therapy often require multidisciplinary combination therapy in clinical practice. Tuina therapy and repetitive transcranial magnetic stimulation (rTMS) have shown potential in modulating neural plasticity and improving depressive symptoms. However, the combined efficacy of these non-pharmacological therapies on PSD and their underlying mechanisms remain underexplored. This study aims to investigate the clinical effectiveness of massage combined with rTMS in treating PSD and explore its impact on brain functional networks and neuroendocrine mechanisms.

**Methods and analysis:**

This study is a non-inferiority randomized controlled trial (RCT). One hundred and twenty-eight participants with PSD will be randomly assigned (1:1) to the intervention group (Tuina + rTMS treatment) and the control group (cognitive behavior treatment). The primary efficacy outcome is the change from baseline to week 2 in Hamilton Depression Rating Scale (HAMD) and Functional Magnetic Resonance Imaging (fMRI). Secondary efficacy outcomes include other assessments of the Mini-Mental State Examination (MMSE), The modified Barthel index (MBI), The National Institutes of Health Stroke Scale(NIHSS), inflammatory factor (IL-6, IL – 17, TNF-*α*, IFN-*γ*, IL-4, IL-10), and Functional near-infrared spectroscopy (fNIRS). Efficacy and scale assessments will be conducted at 1 month and 3 months after the completion of treatment.

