## Methods and analysis

### Study design

This study is a single-center, parallel-design, analyst-blinded, randomized, controlled trial. A total of 128 PSD patients will be recruited and randomly assigned them in a 1:1 ratio to an intervention group and a control group. The intervention group will receive Tuina combined with rTMS, while the control group will undergo CBT. The study lasts 14 weeks and includes baseline assessments, a 2-week treatment phase, and a 3-month follow-up period. This study protocol has been developed in compliance with the SPIRIT 2013 guidelines for clinical trial reporting and adheres to the ethical principles outlined in the Declaration of Helsinki (version 2013). The study flowchart is presented in Figure 1, and the detailed study schedule is outlined in Table 1. The trial was registered at Chinese Clinical Trial Registry, https://www.chictr.org.cn/, identifier ChiCTR2400085310.

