### Sample size calculation

The sample size for this study was calculated based on data from a previous clinical trial (20), in which the HAMD score was 9.90 ± 4.61 in the Tuina therapy group and 13.24 ± 4.36 in the conventional rehabilitation group. The combined standard deviation (*σ*) was 4.49. To detect a difference between group means (*Δ* = 2.5) with a statistical power of 80% (*β* = 0.2, corresponding to Zβ = 0.84) and a significance level of 0.05 (*α* = 0.05, corresponding to Zα/2 = 1.96), the required sample size per group was calculated using the following formula, with calculations performed in G*Power software to ensure adequate statistical power:

$$n=\frac{{\left(Z_{\alpha /2}+Z_{\beta }\right)}^{2}\cdot 2\sigma^{2}}{\Delta^{2}}$$

Thus, each group requires approximately 51 participants. Considering a 20% dropout rate, the adjusted sample size is 64. Therefore, a total of 64 participants per group will be required, resulting in a total sample size of 128 participants.

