### Statistical analysis

#### Statistical analysis of scales and general information

All statistical analyses will be performed using SPSS version 26.0. Continuous variables will be presented as mean ± standard deviation (SD) and compared using independent t-tests or Mann–Whitney U tests based on data normality. Categorical variables will be expressed as frequencies and percentages and analyzed using chi-square or Fisher’s exact tests. Missing data will be handled using multiple imputation. To control for potential confounders, a multivariate regression analysis will be conducted. A two-tailed *p*-value < 0.05 will be considered statistically significant.

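### The abstract labels the trial non-inferiority, but its sample size and decision rule are those of a superiority trial and no margin is stated

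*Protocol article*

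**What the plan says.** The abstract, under Methods and analysis, states "This study is a non-inferiority randomized controlled trial (RCT". It sets Tuina plus rTMS against cognitive behavioural therapy (CBT), an active comparator.

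The term does not recur in the body of the article:

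- **Study design** calls the trial a "single-center, parallel-design, analyst-blinded, randomized, controlled trial" and names no non-inferiority hypothesis.
- **Sample size calculation** is done "To detect a difference between group means" of 2.5 HAMD points, with an SD of 4.49, 80% power and alpha 0.05, "corresponding to Zα/2 = 1.96". The planning data come from an earlier trial of Tuina (9.90 ± 4.61) against usual care ("13.24 ± 4.36 in the conventional rehabilitation group"). Neither arm of that trial received CBT.
- **Statistical analysis of scales and general information** says that continuous variables are "compared using independent t-tests or Mann–Whitney U tests based on data normality". The same section ends with a two-tailed 0.05 significance threshold.

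No non-inferiority margin appears anywhere in the article.

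**The concern.** Non-inferiority and superiority are different hypotheses. A superiority test asks whether the difference from CBT can be told apart from zero. A non-inferiority test asks whether a loss against CBT larger than a stated margin can be excluded. The second question cannot be posed without the margin.

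What is at stake is the meaning of a non-significant primary result. Against an active comparator that outcome is quite possible, and the abstract's label invites it to be read as showing that the new treatment is no worse. The plan as written gives no basis for that reading, and a margin chosen after the data are seen would not supply one. The label also leaves unclear which hypothesis the stated 80% power refers to.

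**Working it through.** **Inputs from Sample size calculation:** difference 2.5, SD 4.49, two-sided alpha 0.05 (z = 1.96), power 80% (z = 0.84), 1:1 allocation, 20% dropout.

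**1. Reproduce the plan's figure.** With the printed formula,

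n = (1.96 + 0.84)² × 2 × 4.49² / 2.5² = 50.6, so 51 per arm.

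For dropout, 51 / 0.80 = 63.75, so 64 per arm and 128 in total. The plan's 51, 64 and 128 are all reproduced. Power at 51 per arm is 80.3% by the normal approximation and 79.5% by the exact t-test. The arithmetic is sound for a two-sided test of a difference of 2.5.

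**2. Ask when the same number would be a non-inferiority calculation.** For margin m, true difference d (positive when the new treatment is worse) and one-sided alpha 0.025,

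n = (1.96 + 0.84)² × 2 × 4.49² / (m − d)².

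This also gives 51 per arm when m − d = 2.5, for example m = 2.5 with d = 0. So the number alone cannot separate the two hypotheses. The text does: it calls 2.5 the difference to be detected, not a loss to be tolerated.

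**3. Non-inferiority power of the planned trial.** The documents give no margin, so these margins are assumptions. With 51 evaluable per arm,

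SE = 4.49 × √(2/51) = 0.889.

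At a true difference of 0, power = Φ(m / 0.889 − 1.96). The third column solves the formula in step 2 for 80% power.

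| Assumed margin (HAMD points) | Power with 51 per arm | Evaluable per arm for 80% power | Per arm after 20% dropout |
|---|---|---|---|
| 1.0 | 20% | 317 | 397 |
| 1.5 | 39% | 141 | 177 |
| 2.0 | 61% | 80 | 100 |
| 2.5 | 80% | 51 | 64 |
| 3.0 | 92% | 36 | 45 |

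The result also depends on the true difference. If the new treatment were truly 1 point better than CBT (d = −1), a margin of 1.5 would again need 51 per arm.

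**4. What each outcome would support under the written rule.**

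- *Significant, favouring Tuina plus rTMS:* superiority is shown, and with it non-inferiority at any positive margin.
- *Not significant:* a difference has not been shown. The 95% confidence interval would extend about 1.96 × 0.889 = 1.74 points either side of the estimate, but with no margin set in advance there is nothing to compare its upper limit with.

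**The case against.** The best defence is that this is one stray word. The design, sample size and analysis sections together describe a coherent superiority trial, and the aims and discussion speak of efficacy and combined effects, not of non-inferiority. That is fair. The non-inferiority claim rests on a single label in the abstract, which is why the simplest remedy is a change of wording.

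A second defence is that the article is condensed and the details may sit elsewhere. This holds for a confidence interval rule and for the choice of analysis sets, which are commonly left to the analysis plan, and their absence is not counted here. It does not hold for the margin. A margin is an input to any non-inferiority sample size, and the article gives its whole derivation (source data, SD, difference, alpha, power, formula, dropout) without one.

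Three stronger readings are tempting, and the documents do not support them:

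- *The trial cannot show non-inferiority at all.* This goes too far, because a significant superiority result would also show it.
- *The sample is too small.* This is not shown. Fifty-one per arm gives 80% non-inferiority power for a margin of 2.5 at no true difference, and smaller margins could be met if the new treatment is truly better.
- *The plan will treat p > 0.05 as proof of non-inferiority.* The article says no such thing. It only leaves that misreading open.

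It is also tempting to judge 2.5 as a margin against the earlier trial's difference of 13.24 − 9.90 = 3.34. That difference is Tuina against conventional rehabilitation. It carries no information on CBT's effect, so it can neither support nor discredit a margin against CBT.

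**Conclusion.** The article contradicts itself on its primary hypothesis. The abstract says non-inferiority, the sample size and significance rule say superiority, and there is no margin. The practical effect is confined to a result that is not significant in favour of Tuina plus rTMS, which could not support the labelled claim against CBT.

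As worded, the 80% power is for detecting a difference of 2.5. For non-inferiority it would be about 80%, 61% or 39% at margins of 2.5, 2.0 or 1.5. Those figures assume the margins, an SD of 4.49, 51 evaluable per arm, one-sided alpha 0.025 and no true difference. The sample size arithmetic itself is correct. The point should be settled before the data are analysed, because it determines what the trial may conclude.

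**What to change.** **If superiority is intended, as the body of the article indicates:**

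- Delete the non-inferiority label from the abstract.
- State the HAMD-17 hypothesis as superiority of Tuina plus rTMS over CBT at week 2, two-sided 0.05, planned difference 2.5.
- Add a sentence that a non-significant result will not be read as non-inferiority or equivalence.

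This is a change of wording and needs no extra participants. The same correction belongs in any other trial document that carries the label; those were not available to check.

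**If non-inferiority is truly intended:** before any outcome data are examined, fix a HAMD-17 margin justified by evidence on CBT's own effect, and state that non-inferiority is concluded only if the 95% confidence limit on the unfavourable side lies within that margin. Then restate the power of the planned 51 evaluable per arm for that margin and for an explicit assumption about the true difference. Waiting only until formal unblinding is too weak a safeguard, since participants and treatment providers know the allocation throughout. The cost depends on the margin. At no true difference, 2.5 keeps 64 per arm, 2.0 needs 100 and 1.5 needs 177 for 80% power after 20% dropout.

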**Discussion:**

This trial will provide reliable evidence on the efficacy of Tuina combined with rTMS in treating PSD and explore its impact on brain functional networks and neuroendocrine mechanisms.

## Introduction

Post-stroke depression (PSD), characterized by low mood and low interest, is the most common complication after stroke. PSD can reduce the quality of life of patients, impair their cognitive function and life ability, and affect their process of rehabilitative treatment (1). Compared to other functional impairments after stroke, PSD is often overlooked (2). Relevant investigation results show that one third of stroke patients are affected by depression (3). PSD can occur at any time after stroke, with the highest prevalence during the first year and decreasing thereafter (4). It is worth noting that PSD is associated with poor outcome and increased mortality. The early diagnosis of PSD presents certain challenges. It relies on scale assessments, which are inherently subjective, and lacks objective diagnostic tools.

Although drug therapy is currently the primary clinical intervention for post-stroke depression, it exhibits numerous limitations (5). The efficacy of antidepressant drugs differs significantly among individuals, with some patients exhibiting poor response to conventional doses. Additionally, their adverse reactions can diminish patient compliance (6, 7). Drug therapy primarily focuses on symptom relief, with limited impact on promoting neuroplasticity and brain function recovery. Therefore, exploring safer complementary and alternative therapies is crucial for the treatment of PSD.

Tuina is a traditional non-drug therapy originating in China, which has demonstrated advantages in the treatment of depressive disorders. This therapy provides holistic regulation of the body, alleviating depressive symptoms while simultaneously addressing accompanying physical discomfort. It is essentially a tactile therapy that induces a pleasant sensory experience, which can alter the excitability and connectivity of brain regions involved in emotional regulation (8). There is research recommending massage as a B-level evidence for the treatment of depression disorders (9). A network meta-analysis has revealed that Tuina and other manual therapy are more effective than pharmacological interventions in reducing depressive symptoms in patients with depression of mild dementia (10). Additionally, multiple clinical studies have reported significant therapeutic efficacy of Tuina in the treatment of depression (11, 12).

Transcranial magnetic stimulation (TMS) is a non-invasive neuroregulation technique that has become a common treatment option for depression (13). Repetitive transcranial magnetic stimulation (rTMS) is a widely used form of TMS, characterized by the delivery of repeated magnetic pulses to specific cortical regions to modulate brain activity. By targeting depression-related brain regions, especially the dorsolateral prefrontal cortex (DLPFC) and associated emotional regulation networks, rTMS improves neural circuit function and promotes neuroplasticity (14). It has been recommended by the American Psychiatric Association (APA), as an effective treatment, particularly for treatment-resistant depression (15). A meta-analysis has demonstrated that rTMS can significantly improve outcomes in patients with PSD (16). Further research is essential to refine stimulation parameters, evaluate the long-term therapeutic effects, and explore the integration of rTMS with complementary approaches to enhance its efficacy.

Non-pharmacological therapies, with their reduced side effects and broader applicability, are gaining increasing attention in the treatment of PSD. Meta-analyses have confirmed their effectiveness, highlighting their potential as valuable therapeutic options (17–19). Among these, Tuina and rTMS have shown promise as separate interventions. Tuina therapy stimulates the spinal cord through peripheral interventions, promoting positive neuroplasticity in central emotional networks and restructuring neural circuits to treat PSD. Previous studies of our research group showed that Tuina improve PSD symptoms and enhance functional connectivity (FC) of hippocampus and thalamus (20). rTMS targets specific brain regions to enhance neural network function and plasticity. Tuina and rTMS act through distinct but potentially complementary mechanisms. While Tuina modulates brain function through bottom-up pathways initiated by peripheral stimulation, rTMS exerts top-down regulation by directly stimulating cortical targets. The combination of these two therapies may produce synergistic effects, contributing to improvements in emotional regulation, cognitive function, and limb function by integrating peripheral and central multi-level therapeutic mechanisms.

Despite advances in non-pharmacological treatments for PSD, the therapeutic potential of combining Tuina and rTMS remains unexplored. This study aims to evaluate the combined efficacy of Tuina and rTMS in improving emotional, cognitive, and functional outcomes in PSD patients. Using fMRI and fNIRS, this study investigates neural network remodeling and circuit reconstruction to elucidate the mechanisms underlying central regulation.

## Methods and analysis

### Study design

This study is a single-center, parallel-design, analyst-blinded, randomized, controlled trial. A total of 128 PSD patients will be recruited and randomly assigned them in a 1:1 ratio to an intervention group and a control group. The intervention group will receive Tuina combined with rTMS, while the control group will undergo CBT. The study lasts 14 weeks and includes baseline assessments, a 2-week treatment phase, and a 3-month follow-up period. This study protocol has been developed in compliance with the SPIRIT 2013 guidelines for clinical trial reporting and adheres to the ethical principles outlined in the Declaration of Helsinki (version 2013). The study flowchart is presented in Figure 1, and the detailed study schedule is outlined in Table 1. The trial was registered at Chinese Clinical Trial Registry, https://www.chictr.org.cn/, identifier ChiCTR2400085310.

**Figure 1 fig1:**
[figure not shown]
Participant flow chart.

**Table 1 tab1:** Study schedule.

Study procedure	Period				
Time point	−1 week	0 week	2 week	6 week	14 week
Entry and administrative					
Eligibility screen	X				
Demographics	X				
Medical history	X				
Informed consent	X				
Randomization	X				
Interventions					
Tuina+rTMS		X	X		
CBT		X	X		
Outcome measures					
HAMD-17		X	X	X	X
fMRI		X	X		
NIHSS		X	X	X	X
MBI		X	X	X	X
MMSE		X	X	X	X
fNIRS		X	X		
Blood parameters		X	X		
Safety evaluations		X	X	X	X
Drug combinations		X	X	X	X
Patient compliance		X	X	X	X
Adverse events		X	X	X	X

### Participant recruitment

This study will be taken place in the inpatient unit of the Rehabilitation Department at Shuguang Hospital, affiliated with Shanghai University of Traditional Chinese Medicine. Recruitment announcements will be made through the hospital’s official social media account to maximize visibility and accessibility for potential participants. Patients will be recruited from the Rehabilitation Department, the Neurology Department, and local community centers. Additional recruitment efforts will include posters and the WeChat platform. Eligibility screening will take place at Shuguang Hospital, conducted by a designated recruitment physician.

### Inclusion criteria

Diagnostic criteria include:

The diagnostic criteria of potential subjects refer to the Chinese Guidelines for Diagnosis and Treatment of Acute Ischemic Stroke 2018 (21), and based on The Chinese Expert Consensus on Clinical Practice for Post-Stroke Depression (22). At least three of the following symptoms must be present and persist for more than 1 week (with at least one of the symptoms from either item 1 or 2):

Frequent occurrence of low mood.Loss of interest in daily activities.Significant reduction in energy or persistent fatigue without any obvious cause.Psychomotor retardation or agitation.Excessively low self-esteem, self-blame, or feelings of guilt reaching delusional severity.Lack of decisiveness, difficulty with associations, or a noticeable decline in cognitive abilities.Recurrent thoughts of death or suicidal ideation, or attempted suicide behavior.Insomnia, early awakening, or excessive sleep.Loss of appetite or significant weight loss.

Age range: 45–80 years.Right-handed.Individuals with mild to moderate depression who score greater than 7, but less than or equal to 24 on the Hamilton Depression Rating Scale (HAMD-17).No consciousness impairment, no aphasia, cardiac function ≥ Grade 3, and stable vital signs.Patients must not have received antidepressant medications, Tuina therapy, or rTMS within the past 3 months.Complete screening and voluntarily sign the informed consent form (if the patient is unable to sign the informed consent due to physical impairments, the family member may sign on their behalf).

### Exclusion criteria

Visual/hearing impairments, dementia (MMSE ≤ 20), cognitive dysfunction, or inability to complete assessments.Personal or family history of psychiatric disorders.Patients with severe suicidal tendencies.Acute (within 2 weeks) or progressive stroke, or severe systemic diseases (severe cardiovascular, hepatic, renal, respiratory, endocrine, or neurological diseases) with unstable vitals.Severe dermatological issues or local skin damage.Contraindications for TMS or MRI, such as pacemakers or metal implants.Use of antidepressant medication during the intervention period.

### Drop-out criteria

Severe complications or worsening of the condition during the trial.Inability to tolerate Tuina or rTMS treatment.Withdrawal from the study or inability to complete the treatment.Development of other conditions deemed by the investigator to make continued participation in the clinical trial inappropriate.

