### Randomization and blinding

Eligible participants will be randomly assigned to either the intervention group (Tuina + rTMS) or the control group (CBT) in a 1:1 ratio. A computer-generated randomization sequence will be prepared using the “proc plan” procedure in SAS 9.4 (SAS Institute Inc.), employing randomly permuted block sizes to ensure balanced group allocation. An independent researcher, uninvolved in recruitment, intervention, or data analysis, will generate the sequence. Each allocation will be concealed in a sequentially numbered, opaque, sealed envelope, securely stored to maintain allocation concealment. At the point of enrollment, the recruiting investigator will open the next envelope in sequence to determine group assignment. To minimize bias, outcome assessors, and statisticians will remain blinded to group allocation throughout the trial. Given the nature of the intervention, it is not feasible to blind PSD participants or treatment providers to group allocation. All participants will receive the same standard information about the study objectives and procedures at baseline without disclosing specific group assignments. Furthermore, both groups will receive interventions with identical frequency, duration, and therapist interaction time to control for nonspecific therapeutic effects. Statisticians, administrators, data collectors, and outcome assessors will be blinded during the study. And blinding will only be broken after data analysis is completed.

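### The drop-out and exclusion rules do not separate stopping treatment from leaving the trial, so randomised patients can be lost for outcome-related reasons that multiple imputation would not correct

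*Protocol article*

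**What the plan says.** The Drop-out criteria section of the protocol article has four items:

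- "Severe complications or worsening of the condition during the trial"
- "Inability to tolerate Tuina or rTMS treatment"
- "Withdrawal from the study or inability to complete the treatment"
- "Development of other conditions deemed by the investigator to make continued participation in the clinical trial inappropriate"

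The Exclusion criteria section lists "Use of antidepressant medication during the intervention period". Antidepressant use in the three months before entry is dealt with separately, under Inclusion criteria.

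On blinding, the Randomization and blinding section says "it is not feasible to blind PSD participants or treatment providers to group allocation"; outcome assessors and statisticians are to be blinded. On incomplete data, the section on scales and general information says "Missing data will be handled using multiple imputation" and gives no model or assumption. The Sample size calculation section raises 51 per group to 64 for 20% dropout. Table 1 schedules HAMD-17 at weeks 0, 2, 6 and 14, with a row for drug combinations at the same visits.

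**The concern.** A rule for stopping study treatment and a rule for leaving the study are different things, and the drop-out list does not tell them apart. Its last item is worded in terms of staying in the trial, and the sample size section treats dropout as lost numbers. Both point towards leaving the study.

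If so, several of the reasons for leaving are related to outcome. Worsening may be the outcome itself. Intolerance of Tuina or rTMS can arise only in the intervention arm. Investigator judgement is exercised in a trial where treatment providers know the arm. The antidepressant line sits among the eligibility criteria, but what it describes cannot be known at enrolment, so applying it means removing a patient already randomised. Starting an antidepressant during treatment is a plausible sign of non-response, although the article does not say so.

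What is at stake is the protection that randomisation gives to the HAMD-17 comparison. The abstract calls the trial non-inferiority, so a shift in favour of the intervention would push towards the hoped-for conclusion.

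**Working it through.** **The plan's own figure.** Inputs from the Sample size calculation section: SD 4.49, difference 2.5, two-sided 0.05, power 80%.

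n = (1.96 + 0.84)² × 2 × 4.49² / 2.5² = 50.6, rounded up to 51 per group. Then 51 / 0.80 = 63.75, rounded up to 64 per group and 128 in total. The stated figures reproduce. The 20% is applied alike to both groups and only as a loss of numbers.

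**Bias formula.** Let a share d of an arm be removed, and let those patients score k HAMD-17 points worse than those who stay. The mean of all randomised patients in that arm is the stayers' mean plus d × k, so the stayers look better by d × k. For the difference, intervention minus CBT:

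bias = −(dT − dC) × k

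where dT and dC are the shares removed from the intervention and CBT arms. A negative value favours the intervention, because lower scores are better.

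**Assumed inputs.** The documents give neither dropout by arm nor k. I take k = 2.25, 4.49 and 6.7, roughly a half, one and one and a half of the plan's SD, and splits that average the planned 20%.

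| Removed, intervention / CBT | k = 2.25 | k = 4.49 | k = 6.7 |
|---|---|---|---|
| 20% / 20% | 0 | 0 | 0 |
| 25% / 15% | −0.23 | −0.45 | −0.67 |
| 30% / 10% | −0.45 | −0.90 | −1.34 |
| 10% / 30% | +0.45 | +0.90 | +1.34 |

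For example, −(0.30 − 0.10) × 4.49 = −0.90. As shares of the planned 2.5, 25%/15% gives 9% to 27% and 30%/10% gives 18% to 54%.

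**Effect on error.** Take no true difference and k = 4.49. The standard error among stayers is 4.49 × √(1/(64(1 − dT)) + 1/(64(1 − dC))), about 0.89 in both unequal cases. The chance of a one-sided 2.5% finding in favour of the intervention is the upper normal tail beyond 1.96 − |bias|/SE. This is about 7% for 25%/15% and about 17% for 30%/10%.

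**Multiple imputation.** Under missing-at-random, imputation predicts the removed patients' scores from patients who stayed and look alike on the observed data. If the reason for removal carries information that those data do not, the bias above remains.

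**The case against.** A reader might infer that the trial will compare completers with completers, that failures will leave unequally, and that the result will favour Tuina plus rTMS. The documents do not support going that far.

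- The article never says that patients who meet these criteria are deleted from the analysis or left unassessed. Planned imputation suggests that patients without scores stay in. A named analysis set is commonly left to the full protocol or analysis plan, and its absence here is no fault. This stands.
- The intolerance item has no counterpart naming CBT, but the next item, on withdrawal or non-completion, covers a CBT patient who cannot continue. The wording differs by arm; the article does not show that exit rates would. This stands.
- It is tempting to apply the 20% dropout allowance to one arm and read off 0.20 × 4.49 = 0.90 points. That is the shift in one arm's mean. The plan allows 20% in each group, and with equal severity the two shifts cancel.
- Worsening is paired with severe complications and may mean medical deterioration more than non-response on HAMD-17. This is possible, but such patients may still differ in prognosis from those who stay.
- The Primary outcomes section mentions a HAMD-17 assessment at week 1, which could help the imputation. It would help in part, if collected, but Table 1 does not schedule that visit.

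What survives is that the rules are stated, not merely left out, and that they concern data collection. A score never collected cannot be recovered by a later analysis plan.

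**Conclusion.** The concern holds as a foreseeable risk written into the rules. Its size and direction cannot be fixed from the documents. As worded, the criteria can take randomised patients out of the trial for reasons related to outcome, in an open-label setting, and one listed exclusion can operate only after enrolment.

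On the assumed inputs the shift in the between-arm difference runs from 0, with equal loss and equal severity, to about 1.3 HAMD-17 points in either direction. A 10 to 20 percentage-point gap in the share removed gives 9% to 54% of the planned 2.5. These figures describe what happens if removed patients' scores are not collected and imputation does not account for why they left. They are not a forecast for this trial.

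**What to change.** Leave every clinical decision about stopping treatment as it is, and change only what follows from it for the data:

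1. State that the drop-out criteria end study treatment and do not end follow-up.
2. Collect HAMD-17 at the scheduled weeks 2, 6 and 14 in all randomised patients who still consent.
3. Move antidepressant use during treatment from the exclusion list to a recorded post-randomisation event; the drug combinations row in Table 1 can hold it.
4. Analyse all randomised patients in their assigned arm.
5. Keep multiple imputation for scores that cannot be obtained, and add a sensitivity analysis that imputes dropouts as worse than observed.

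The cost is protocol wording and some visits after early stopping. The sample size stays at 128. The estimated effect may be slightly smaller, because patients who stopped treatment then count. The change should be made while patients are still being followed.
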